### Scientific hypothesis

One hypothesis is that an advanced quality improvement program (AQIP) significantly improves clinical outcomes in persons with type 2 diabetes compared to a usual quality improvement program (UQIP). Subgroup analyses can analyze the effect of the program in the two intervention arms using cut-off values. The second hypothesis is that persons with type 2 diabetes who make use of a DCT will have significantly better outcomes compared to non-users of the DCT, regardless of their intervention arm.

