### Participants

All 379 active primary care physicians (PCPs) in the project region are invited to participate in the project. These PCPs work in a semi-rural setting with 357,000 inhabitants and serve predominantly Caucasian patients with type 2 diabetes mellitus. PCPs provide care for approximately 80% of patients with type 2 diabetes, and are often the sole providers of care. The only inclusion criterion for the providers is agreeing to recruit all patients with type 2 diabetes mellitus to prevent selection bias. In addition, PCPs will be asked to screen more systematically for new type 2 diabetes mellitus patients during the seven months after registration begins. Diabetes is defined in accordance with the 2003 ADA criteria [35] with PCPs making the final diagnosis.

Only patients with type 2 diabetes mellitus will be included in the study, regardless of age. Patients who cannot provide informed consent will be excluded from the study.

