**Patient**		
Lack of adhere to treatment regimen and clinical inertia related to:*e.g*. Limited motivation or resistance to adopting lifestyles that support optimal disease care.		
	Usual Quality Improvement Program (UQIP)	Advanced Quality Improvement Program (AQIP)
Patient education	Medical assessments and education upon referral of the PCPs by diabetologist or DCT	Medical assessments and education upon referral of the PCPs by diabetologist or DCT (DCT)
	= internist, nurse educator, dietician and ophthalmologist	= internist, nurse educator, flying educator, dietician, ophthalmologist and health psychologist
Promotion of self-management	----	Education of patients in practice (by flying educator)
	----	Education at patient's home (by flying educator)
	----	Counseling by health psychologist
	----	Structured educational materials from DCT
	----	Structured educational materials from community organizations
	----	Group educational sessions for patients and family members
	----	Free access to blood monitoring tools for self-management

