### Randomization and allocation concealment

After recruitment, a researcher not involved in the study and blind to the identity of the practices will perform a randomization (by computer-generated numbers) stratified by practice size (solo/duo/group practice) and the presence or absence of an electronic medical recording system. To minimize the possibility of selection bias, all patients within a cluster will be included. Blinding will be ensured for the participating patients, but is not possible at the physician level.

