### Data collection

These practices have no pre-existing registers of diabetic patients. Patients with type 2 diabetes mellitus will be identified using physician memory, searching computerized records, and laboratory lists of patients with increased glycemia or registered glycosylated hemoglobin. Baseline data will be collected over a seven-month period. PCPs will be asked to perform a complete examination and blood analysis at the patient's first visit and to complete a paper form. Identified patients without a visit during the first three months of the project will be invited to participate. The completeness of data capture will be double-checked by a data monitor. Final data will be collected over a seven-month period, with call-backs for non-compliant patients. Patient data sheets include socio-demographic and biomedical data. PCPs will need to indicate whether diabetes is treated by the PCP or in a diabetes clinic.

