### Statistical analysis

Statistical analyses will be performed using an intent-to-treat approach with a multilevel model. Linear and generalized linear mixed models will be used to account for the clustered nature of the data, *i.e*., patients clustered within PCPs, and repeated assessments clustered within patients. Such models measure how outcomes change over time within patients and whether these changes depend on patient and/or PCP's characteristics, such as the intervention program or DCT use (see hypothesis two). DCT use is defined as having at least one consultation with a member of the team besides the health psychologist and the traveling educator, which are only available for AQIP patients.

We will use generalized estimating equations (GEE), an extension of the quasi-likelihood approach, to test for differences in the evolution of the primary and secondary endpoints for all patients and within the intervention arms. For binary variables, we use the exponential inverse transformation to obtain the 95% confidence interval for the odds ratio.

Subgroup analyses (see hypothesis one) can distinguish intervention effects using different cut-off values. For HbA1C, three subgroups are defined: patients with HbA1c < 7%; HbA1c ≥ 7% and < 8%; and HbA1c ≥ 8%. For SBP, four subgroups are defined: patients with SBP ≤ 130 mmHg; SBP > 130 mmHg and ≤ 140 mmHg; SBP > 140 mmHg and ≤ 160 mmHg; and SBP > 160 mmHg. For LDL-C, four subgroups are defined: patients with LDL-C < 100 mg/dl; LDL-C ≥ 100 mg/dl and < 115 mg/dl; LDL-C ≥ 115 mg/dl and < 130 mg/dl; and LDL-C > 130 mg/dl.

Linear mixed models with subject-specific intercepts and slopes are used to test whether subject-specific evolutions are related to initial parameters. HbA1c will be transformed logarithmically to meet the parametric assumptions of the statistical models. All analyses will be performed using SAS, version 9.

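### Hypothesis two counts diabetes-clinic patients as non-users of the diabetes care team, so the team is compared with a mixture of primary care and other specialist care

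*Protocol article*

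**What the plan says.** All references are to the protocol article.

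- **Scientific hypothesis.** The second hypothesis, which pools both arms, is about patients "who make use of a DCT will have significantly better outcomes compared to non-users of the DCT".
- **Statistical analysis.** The exposure is fixed: "DCT use is defined as having at least one consultation with a member of the team besides the health psychologist and the traveling educator". DCT use enters the mixed model as a patient or PCP characteristic. Non-use is not defined separately.
- **Participants.** On enrolment: "The only inclusion criterion for the providers is agreeing to recruit all patients with type 2 diabetes mellitus". The only patient exclusion stated, apart from not having type 2 diabetes, is inability to give consent.
- **Randomization and allocation concealment.** The same rule is repeated: "all patients within a cluster will be included".
- **Data collection.** The patient data sheet carries one item on place of care: "PCPs will need to indicate whether diabetes is treated by the PCP or in a diabetes clinic". No stated analysis uses this item.

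**The concern.** The section on team changes describes the DCTs as working in support of PCPs. The informative question is therefore how PCP-managed patients fare with the DCT compared with PCP-managed patients without it. A patient whose diabetes is already treated in a clinic is not in that second group, yet under the stated definition is counted there.

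At stake is what a result for hypothesis two would mean. If clinic patients improve less than PCP-managed non-users, perhaps because their disease is more advanced, the DCT looks better than it is. If clinic care works about as well as the DCT, a real benefit of the DCT is diluted. The mixed model accounts for clustering of patients and of repeated measurements. It does not correct the composition of the reference group.

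**Working it through.** The article gives no figure for this comparison; its sample-size statement concerns the randomized arms. The check is therefore one of definitions, followed by an illustration.

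**Definitions, in order**

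1. The contrast is users against non-users, pooled over both arms (Scientific hypothesis).
2. Use needs one qualifying team consultation, so non-use is the complement among all enrolled patients (Statistical analysis).
3. All type 2 patients of a practice are enrolled, and specialist care elsewhere is no ground for exclusion (Participants; Randomization and allocation concealment).
4. Clinic-treated patients are foreseen among those enrolled, because the form asks about them (Data collection). Table 2 also distinguishes the project DCT from an in-hospital team in secondary care.
5. Hence a clinic-treated patient without a qualifying DCT consultation is a non-user.

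**Illustration of size**

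Let *c* be the clinic-treated share of enrolled patients and *u* the share of PCP-managed patients who use the DCT. Assume that no clinic-treated patient uses the DCT. The clinic share of non-users is

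*s* = *c* / [*c* + (1 − *c*)(1 − *u*)].

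The article gives neither *c* nor *u*. The ranges below are assumptions.

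| *c* | *u* = 20% | *u* = 40% |
|---|---|---|
| 5% | 0.05/0.81 = 6.2% | 0.05/0.62 = 8.1% |
| 10% | 0.10/0.82 = 12.2% | 0.10/0.64 = 15.6% |
| 20% | 0.20/0.84 = 23.8% | 0.20/0.68 = 29.4% |

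Let *U*, *P* and *C* be the mean change in the at-target proportion for DCT users, PCP-managed non-users and clinic-treated patients. The planned contrast is

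*U* − [(1 − *s*)*P* + *sC*] = (*U* − *P*) + *s*(*P* − *C*).

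The last term is the distortion. With *s* from 6.2% to 29.4%:

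- *P* − *C* = 10 points: distortion of 0.6 to 2.9 points in favour of the DCT.
- *P* − *C* = 20 points: 1.2 to 5.9 points in favour of the DCT.
- *P* − *C* negative: the same amounts against the DCT.

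Dilution is a special case. If clinic care has *f* times the DCT effect, the observed contrast is (1 − *sf*) times the true one. A true 10-point difference would appear as 9.7 to 8.5 points for *f* = 0.5, and as 9.4 to 7.1 points for *f* = 1.

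These shifts are not turned into false-positive rates. That would need the variance of the change and the clustering of DCT use within practices, neither of which the article gives for this comparison. Treating patients as independent would not be credible beside the article's assumed intracluster coefficient of 0.6.

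**The case against.** **The hypothesis as worded is internally consistent.** Users against all others is a legitimate contrast in a pragmatic trial, and the article never says that non-users lack specialist support. This stands in part: there is no contradiction in the text. But a legitimate contrast can still be hard to interpret, and the article's own account of the DCT as support for PCPs makes the mixed reference group a poor match to its purpose.

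**The analysis plan may deal with it.** The model's list of characteristics is open-ended, and place of care is collected on purpose. Covariate lists are indeed commonly left to a fuller document. Here, however, the article itself fixes the contrast and the exposure definition, and it settles one borderline case (visits to the psychologist and the traveling educator). Followed as written, these choices give the mixed group.

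**Three stronger readings are tempting and not supported.**

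- A reader might infer from Table 2 ("Medical assessments and education upon referral of the PCPs by diabetologist or DCT") that patients referred to a diabetologist outside the team are also misplaced. The article does not say that this diabetologist is outside the team. The account of patient education mentions internists and diabetologists together, and a diabetologist supervises the DCTs. Whether such a visit counts as DCT use is unclear.
- A reader might take the statement that PCPs care for about 80% of type 2 patients to mean that 20% of those enrolled are clinic-treated. The figure is not a share of enrolled patients; many of the rest may not be in these practices' samples at all.
- A reader might infer that the comparison is biased towards the DCT. The sign depends on how clinic patients fare, which the article does not show.

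Why PCPs refer some patients to the DCT and not others is a separate and possibly larger weakness of this non-randomized comparison. The present point does not resolve it.

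**Conclusion.** The point holds for clinic-treated patients. Under the stated contrast and definition they are non-users, and no stated step separates them. The result of hypothesis two would mix two comparisons.

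The size and direction of the distortion cannot be determined from the documents. The illustrative shift of 0.6 to 5.9 points, in either direction, rests wholly on assumed clinic shares of 5–20%, DCT uptake of 20–40%, gaps of 10–20 points, and no DCT use by clinic patients. At a 5% clinic share and a 10-point gap it is below 1 point. The randomized comparison under hypothesis one is not affected. This is a cheap improvement to a secondary, observational comparison and does not threaten the trial's main result.

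**What to change.** In the Statistical analysis section, for hypothesis two:

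1. Run the main analysis in patients whose baseline data sheet records that the PCP treats their diabetes. Apply the restriction equally to DCT users and non-users.
2. Report clinic-treated patients as a separate group.
3. Keep the all-patient users-versus-non-users contrast as a sensitivity analysis.
4. Do not remove non-users because of referrals made during the project. That would condition on an event after baseline and on one side only. If deteriorating patients are the ones referred, it would leave a selectively healthier reference group. The article also does not show that such referrals are recorded.

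The change takes a sentence or two and uses an item already on the data sheet. The article does not tie that item to one collection round, so the text should say that the baseline entry is used. The downside is fewer patients in the hypothesis-two comparison. The intent-to-treat analysis of hypothesis one stays as it is.

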## Methods

### Study design

The study is an open pragmatic cluster randomized trial with before/after measurements and two intervention arms. A cluster design is necessary because randomization is performed on a practice level, the intervention happens on the physician level, but a large part of the data are analyzed at the patient level. The implementation period of the trial is 18 months.

### Participants

All 379 active primary care physicians (PCPs) in the project region are invited to participate in the project. These PCPs work in a semi-rural setting with 357,000 inhabitants and serve predominantly Caucasian patients with type 2 diabetes mellitus. PCPs provide care for approximately 80% of patients with type 2 diabetes, and are often the sole providers of care. The only inclusion criterion for the providers is agreeing to recruit all patients with type 2 diabetes mellitus to prevent selection bias. In addition, PCPs will be asked to screen more systematically for new type 2 diabetes mellitus patients during the seven months after registration begins. Diabetes is defined in accordance with the 2003 ADA criteria [35] with PCPs making the final diagnosis.

Only patients with type 2 diabetes mellitus will be included in the study, regardless of age. Patients who cannot provide informed consent will be excluded from the study.

### Intervention

The UK Medical Research Council (MRC) framework for the development and evaluation of complex interventions for randomized control trials (RCT) is used as a theoretical guide to designing the intervention [6]. The MRC framework allows for the development of a high-quality study design, execution, generalizability of the results, and outlines five key phases for intervention development: a preclinical/theoretical phase, a modeling phase, a phase of exploratory trials prior to the randomized controlled trial (RCT), the trial itself, and long-term implementation [36]. All phases except phase two (exploratory trial phase) and phase five (long-term implementation phase) are incorporated here. A detailed overview is provided in Table 1.

**Table 1 T1:** The MRC Framework applied for the development and evaluation of a complex intervention in diabetes care.

**Phases**			
**Phase I- Preclinical theory (Why should the intervention work?)**			
**Content**	**Methods**	**Results**	**Publications**
- Collecting evidence on the effectiveness of multifaceted diabetes intervention programs – Identification of evidence on appropriate outcome indicators - Influence of local context	Review of systematic reviews on diabetes care programs in primary care, outpatient, community and hospital settings to identify: conceptual backgrounds of programs, goals, settings, type of program, type of interventions, type of indicators, (cost) effectiveness of programs and interventions	Overview of best choice of interventions and indicators, selection of conceptual model, overview of major confounders, overview of strategic design issues, overview of barriers to high-quality diabetes care at the macro, meso and micro level	[37]
			
**Phase II- Modeling (How does the intervention work?)**			
**Content**	**Methods**	**Results**	**Publications**

- Understanding of the pathways by which the problem is caused and sustained - Exploration of whether the pathways are amenable to change and, if so, at which points - Quantification of the potential for improvement (estimates of likely effect size) - Program development	- Stakeholder interviews to identify and understand barriers to high-quality diabetes care in the Belgian health care system and multidisciplinary team meetings to discuss program development	- Definition a multifaceted intervention/implementation strategy and outcome-indicators and local adaptation of the treatment protocol	[41]
			
**Phase III – Exploratory Trials (not performed)**			
			
**Phase IV – Randomized Controlled Trial**			
The Diabetes Project Leuven (cluster randomized trial)			
			
**Phase V – Long Term Implementation (not performed)**			

### Preclinical phase of the MRC framework

This phase involves exploration of the relevant theory and evidence to refine the underlying hypotheses, conceptual model, interventions, and indicators. We have previously performed a review of systematic reviews for this purpose [37]. A total of 21 systematic reviews (1989–2006) were included in the review and represented 185 diabetes care programs. Conceptual background, goals, settings, type of programs, type and number of interventions, type and number of indicators, and (cost) effectiveness were evaluated in both the 21 systematic reviews and the individual diabetes care programs. The program is further built on the CCM [8,9] and principles of integrated care. As there is no unambiguous definition of integrated care, we further build on the definitions of Ellrodt and colleagues [38], Mur-Veeman and colleagues [39], and the Disease Management Association of America (DMAA) [40]. We consider integrated care as 'an organizational process of continuous coordination of evidence-based and relevant interventions across the entire health care delivery system and care continuum that seeks to maximize quality of care tailored to the needs of every individual patient while minimizing costs'.

Besides exploring relevant theory and evidence, the local context in terms of existing national and regional governmental policies, characteristics of the region, and perceived barriers to high-quality diabetes care were extensively studied with regard to their impact on the content and execution of the study protocol. We have previously organized stakeholder interviews, including a representative group of 18 Belgian opinion leaders and experts in diabetes care [41].

### Modeling phase

In the modeling phase, we delineated the components of our complex intervention and the underlying mechanisms by which they influence the outcomes. We sought to understand the pathways by which the problem is caused and sustained, including all barriers to high-quality diabetes care. We also explored whether the pathways were amenable to change, and if so, at which points. Finally, we estimated potential for improvement in both process and primary outcomes. This analysis produced the best achievable combination of intervention components, implementation strategies, and intensities of care delivery, as well as the identification of feasible and valid outcome measures.

### Interventions

Two separate groups are defined: the first group will receive a usual quality improvement program (UQIP), and a second group will receive an advanced quality improvement program (AQIP). Physicians can make use of program services on a voluntary basis.

The UQIP arm will aim to improve adherence to evidence-based guidelines and to reduce the rate of clinical inertia in PCPs. The term 'usual' is applied because these interventions address the principal factors contributing to clinical inertia (physician, patient, and office system factors) and represent standard requirements for what is considered quality of diabetes care in most health care systems according to international clinical guidelines [42], and theoretical frameworks on quality of diabetes care in particular [43]. The first intervention arm is innovative to the Belgian healthcare system and adds to available insights from the international literature on how to address clinical inertia in diabetes care.

The AQIP arm will receive similar interventions, but will also include supplementary and experimental interventions that extensively focus on behavior changes in patients and providers. Interventions that focus on the patient aim at a more active involvement of the patient in his/her treatment regimen, with a special focus on lifestyle attitude changes. Improvements in 'patient empowerment' will further decrease clinical inertia by increasing the patient's willingness to intensify his/her treatment [44,45]. Interventions that target the PCP focus on improvements in communication patterns with patients, interdisciplinary shared care, and involving PCPs in community campaigns. This multi-factorial approach, with a focus on patient, provider, and organizational aspects of care, is fully in line with the latest insights and findings on high-quality chronic care, and high-quality diabetes care in particular [9,19,46-53].

The differences between the AQIP and the UQIP are outlined further below and in Table 2.

**Table 2 T2:** Overview of components of the Usual Quality Improvement Program (UQIP) and Advanced Quality Improvement Program (AQIP).

**Patient**		
Lack of adhere to treatment regimen and clinical inertia related to:*e.g*. Limited motivation or resistance to adopting lifestyles that support optimal disease care.		
	Usual Quality Improvement Program (UQIP)	Advanced Quality Improvement Program (AQIP)
Patient education	Medical assessments and education upon referral of the PCPs by diabetologist or DCT	Medical assessments and education upon referral of the PCPs by diabetologist or DCT (DCT)
	= internist, nurse educator, dietician and ophthalmologist	= internist, nurse educator, flying educator, dietician, ophthalmologist and health psychologist
Promotion of self-management	----	Education of patients in practice (by flying educator)
	----	Education at patient's home (by flying educator)
	----	Counseling by health psychologist
	----	Structured educational materials from DCT
	----	Structured educational materials from community organizations
	----	Group educational sessions for patients and family members
	----	Free access to blood monitoring tools for self-management

